### Aims

The aims of this study are as follows:
Verify the effects of BFR-RT on the knee extensor strength of LC patientsVerify the effects of BFR-RT on the vastus lateralis muscle cross-sectional area, fiber Pennation angle, and fascicle lengthVerify the effects of BFR-RT on the functional performance and risk of falls in LC patientsVerify the retention of BFR-RT effects after 12 weeks of protocol cessation (24 weeks)Verify whether BFR-RT results in adverse events in LC patients

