## Assessments

### Primary outcomes

#### Maximal dynamic strength test (1-RM)

Maximal dynamic strength will be tested using one-repetition maximum tests (1-RM). Bilateral 1-RM tests will be performed on a knee extension machine, according to the protocol of Brown and Weir [26]. Initially, a warm-up of 5 min will be performed on a cycloergometer at 20 km·h^− 1^. Then, a specific warm-up for the assessed muscles will be performed using eight repetitions, followed by three repetitions at 50% and 70% of an estimated 1-RM, respectively. A rest interval of 2 min will be allowed between sets. Following warm-up, the 1-RM test will be initiated. Participants will perform both concentric and eccentric phases of the movement. An attempt will be considered successful if complete knee extension (~ 170°) is achieved. Up to five attempts will be allowed, with a rest interval of 3 min between attempts.

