#### Muscle cross-sectional area (CSA)

Vastus lateralis (VL) muscle cross-sectional area (CSA) will be assessed using an ultrasound (US) machine. Procedures similar to Lixandrão et al. [27] will be adopted. Participants will be instructed to abstain from vigorous physical activities for at least 72 h. Following their arrival, participants will lay in a supine position for 15 min to allow fluid shifts to occur. Images will be collected using the US B-mode with a 7.5 MHz probe (Samsung, MySono U6, industria e comércio Ltda. São Paulo, Brazil). Surface gel will be applied to promote acoustic coupling while avoiding dermal deforming. The distance between the greater trochanter and the lateral epicondyle will be manually calculated, and the CSA will be obtained at the 50% point. Sequential markings will be made on participants’ skin to guide probe movement, and images will be acquired every 2 cm. Following data acquisition, VL CSA will be reconstructed according to Reeves et al. [28], whereby images will be sequentially opened and rotated using PowerPoint version 2007 (Microsoft, Redmond, WA, USA), until the full muscle area is visible. The CSA value will be assessed using the ImageJ polygonal tool. Each muscle area will be reconstructed two times, and the mean will be considered the true CSA value.

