## Data analysis

Following visual inspection, data normality will be assessed using the Shapiro-Wilk test. In case of normal distribution, a one-way repeated measures analysis of variance (ANOVA) will be implemented to test for differences in baseline values. Then, a mixed model will be applied for each dependent variable (Child-Pugh class, MELD score, SF-36 and FSS scores, dietary records, TUG, 6MWT, SRT, 1-RM, CSA, PA and FL), having group (BFR-RT and CTRL) and time (0 W, 12 W and 24 W) as fixed factors, and participants as random factors. In case of non-normal data distribution, a Kruskal–Wallis test will be implemented to test for differences in baseline values. Then, the Friedman test will be used to analyze repeated measures. To avoid multiplicity interference on data analysis, adjusted *p* values will be calculated for all variables. Adjusted *p* values will be calculated using Hommel’s procedure, and both adjusted and non-adjusted values will be reported. Additionally, within-group (0-12 W and 0-24 W changes) and between-group effect sizes will be calculated using Cohen’s *d* [33] for each outcome. Finally, the minimal clinically important difference will be analyzed with distribution-based methods [34]. Statistical analysis will be carried out using SAS 9.3 software (SAS institute Inc., Cary, NC).

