## Discussion

LC was reported as the 14th most common cause of death worldwide in 2012, resulting in 1.03 million deaths per year [35], with sarcopenia affecting up to 70% of the patients afflicted by LC [3]. If proven efficient in countering sarcopenia onset or reducing sarcopenia progression, new therapeutic options (e.g., BFR-RT) could help reduce the treatment costs of patients with LC.

As such, the present study aims to verify whether BFR-RT will result in important improvements in muscle strength and mass in patients with liver cirrhosis, as well as verifying any significant differences in functional performance and risk of falls. In addition, the LC Child-Pugh class and MELD score will be evaluated in order to determine BFR-RT safety and effects on the disease’s symptoms. To our knowledge, this will be the first intervention study to investigate BFR-RT in this population. Considering that current evidence shows BFR-RT is a safe method, even for frail populations [15, 17, 18], we believe BFR-RT will result in important increases in muscle mass and strength, accompanied by increases in functionality, with no negative outcomes on cirrhosis condition. There are some limitations to this study. The limited follow-up period prevents us from drawing conclusions about the long-term effects of the proposed intervention. Second, we opted to limit our sample to patients without severe LC complications (i.e., Child-Pugh class B and C and MELD > 15), limiting our ability to generalize our results to patients with decompensated LC.

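### One Hommel adjustment over all 12 listed variables costs 1-RM and CSA power unless effects are very large, and the deciding p value is not named

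*Protocol article*

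**What the plan says.** All references are to the protocol article.

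- **Primary outcomes** has two entries: 1-RM ("Maximal dynamic strength will be tested using one-repetition maximum tests (1-RM)") and CSA ("Vastus lateralis (VL) muscle cross-sectional area (CSA) will be assessed using an ultrasound (US) machine"). Child-Pugh class, MELD and the remaining measures come under Secondary outcomes and the subsections after it.
- **Data analysis** names the dependent variables in a single list: "Child-Pugh class, MELD score, SF-36 and FSS scores, dietary records, TUG, 6MWT, SRT, 1-RM, CSA, PA and FL". It then brings in Hommel's procedure against multiplicity and says of the adjusted p values: "values will be calculated for all variables". No separate primary family, order of testing or exemption is given.
- The same section adds that "both adjusted and non-adjusted values will be reported". It does not say which set supports the conclusion.
- **Discussion** gives two of the listed variables a safety role: "the LC Child-Pugh class and MELD score will be evaluated in order to determine BFR-RT safety".
- **Aims** includes a separate safety aim, "Verify whether BFR-RT results in adverse events in LC patients". Adverse events are not in the list of modelled and adjusted variables.

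**The concern.** Naming two primary outcomes normally means that they carry the confirmatory claim and that other variables do not affect their error control. A single family of 12 gives that distinction no role in the inference. A real gain in strength or CSA then has to clear a hurdle raised by, for example, null results for pennation angle or dietary records, although none of the listed aims concerns diet.

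For Child-Pugh and MELD the adjustment works in the opposite direction from caution. The Background hypothesises that the liver condition will not get worse, so a non-significant result is the hoped-for one, and inflating the p value makes it more likely.

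Finally, adjusted and unadjusted values can disagree. If neither is named as decisive in advance, the choice could be made after the results are known.

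**Working it through.** **Is there a figure to reproduce?** No. The article gives a target of 30 participants but no alpha, power, effect size or SD. Every power figure below is therefore conditional.

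**Inputs**
- n = 15 per arm: 30/2. The total is from Design overview; equal allocation is an assumption.
- Family size m = 12: Child-Pugh, MELD, SF-36, FSS, diet, TUG, 6MWT, SRT, 1-RM, CSA, PA and FL, with SF-36 and diet counted once each. If SF-36 is scored as eight domains (an assumption), m = 12 − 1 + 8 = 19.
- Assumed: two-sided alpha 0.05, no dropout, a two-sample t test at one time point, and both primaries with the same standardised effect d.

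**Step 1: closed-form anchor.** Power of a single t test comes from the noncentral t distribution with df = 2n − 2 = 28 and noncentrality d√(n/2). At d = 1.0 the noncentrality is √7.5 = 2.74. Power is 75% at alpha 0.05 and 37% at 0.05/12 = 0.0042. Hommel is never less powerful than this Bonferroni level, so 37% is a floor for m = 12.

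**Step 2: Hommel itself.** Let j be the largest number for which the j largest p values all satisfy p₍m−j+k₎ > kα/j for k = 1, …, j. Hypotheses with p ≤ α/j are rejected; if no such j exists, all are rejected. I simulated 20,000 trials per row with pairwise correlation 0.3. The code matched the standard statsmodels routine exactly. In the last two columns, either all ten other variables are null, or the seven efficacy secondaries (SF-36, FSS, TUG, 6MWT, SRT, PA, FL) also respond at d.

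| d | Unadjusted | Hommel over 2 primaries | Hommel over 12, others null | Hommel over 12, seven respond |
|---|---|---|---|---|
| 0.8 | 56% | 51% | 20.6% | 24.5% |
| 1.0 | 75% | 72% | 37.5% | 44.9% |
| 1.5 | 98% | 98% | 83.4% | 90.5% |
| 2.0 | 100% | 100% | 98.7% | 99.6% |

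The loss against a two-primary family is about 26–30 points at d = 0.8, 27–34 at d = 1.0, 7–14 at d = 1.5, and about 1 point or less at d = 2.0. Correlations of 0 and 0.5 gave similar figures: at d = 0.8, 21–23% over 12 variables against about 51% over two. With m = 19, power at d = 1.06 (the effect with 80% unadjusted power) is 37–42%, against 44–49% for m = 12 in the same runs.

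**Step 3: safety scores.** One safety variable worsens, both primaries respond at d = 1.06, the rest are null, and the correlation is 0.3. The unadjusted test detects a worsening of 0.8 SD in about 57% of trials and the Hommel-adjusted test over 12 in about 22%. For 1.06 SD the figures are 80% and 45%.

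**Step 4: do the two sets of p values differ in what they protect?** With no effects at all and correlation 0.3, about 40% of simulated trials have at least one of 12 unadjusted p values at or below 0.05, against about 5% after Hommel.

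**The case against.** Several points on the other side have force.

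- **Hommel over all endpoints is valid.** It controls family-wise error and is conservative, not wrong. That stands. The criticism is that it spends error control on variables that carry no confirmatory claim.
- **The power loss depends on the effect size.** A reader might infer that the plan halves primary power. The article gives no effect size, and the trial's own hypothesis expects functional gains too, which helps Hommel. A loss of about half or more appears only at d of about 1 or below, and at d = 1.0 it shrinks to nearly 40% if seven secondaries respond. At d = 2.0 it almost vanishes. The planned mixed model over three time points would also shift the absolute figures.
- **Harm is not hidden.** A reader might infer that the adjustment masks harm signals. The article does not support that: unadjusted p values and effect sizes are also reported, adverse events are outside the adjusted list, and a medical professional screens participants at each time point. The fall in detection applies only if the adjusted value is the one read.
- **The 40% false-positive figure is not the plan's error rate.** It matters only if unadjusted values are allowed to decide.
- **The sentence could mean adjusting contrasts within each variable.** Coming after one list of 12, the all-variables wording favours a single family. On the other reading, the two primaries would have no adjustment against each other, and the deciding p value would still be open.
- **An unseen analysis plan may name the deciding p value.** That is possible, and the gap alone would be a weak point. The scope of the adjustment, however, is stated in the article and is not left open.

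**Conclusion.** The point holds in limited form. On its natural reading, the plan puts 1-RM and CSA in one Hommel family with ten other variables, including dietary records and two scores used to judge safety, and does not say whether adjusted or unadjusted values decide. The cost to the primaries is substantial at d = 0.8 to 1.0, modest at d = 1.5 and negligible at d = 2.0. These sizes rest on 15 per arm, two-sided 0.05, no dropout and a single-time-point comparison; dropout would lower the absolute power figures. The effect on Child-Pugh and MELD is a reduced chance of declaring a worsening if adjusted values decide. It is not concealment. Neither a general halving of power nor a masking of harm can be read from the article.

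**What to change.** In Data analysis:

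1. Define the Hommel family as the two between-group contrasts at 12 weeks, for 1-RM and CSA, and state that these adjusted p values decide the primary conclusion.
2. Treat the secondary efficacy variables as a separate family, or report them as estimates with 95% confidence intervals.
3. Read Child-Pugh and MELD from unadjusted estimates with confidence intervals, and state that a non-significant difference is not evidence of safety.
4. Report dietary records descriptively, outside the tested family.

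This changes analysis wording only, with no new data or participants. Trial status says recruitment was still under way at submission, so the change could be made before analysis. The price is that secondary results carry a weaker claim, because they no longer share family-wise control with the primaries.

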## Discussion

LC was reported as the 14th most common cause of death worldwide in 2012, resulting in 1.03 million deaths per year [35], with sarcopenia affecting up to 70% of the patients afflicted by LC [3]. If proven efficient in countering sarcopenia onset or reducing sarcopenia progression, new therapeutic options (e.g., BFR-RT) could help reduce the treatment costs of patients with LC.

As such, the present study aims to verify whether BFR-RT will result in important improvements in muscle strength and mass in patients with liver cirrhosis, as well as verifying any significant differences in functional performance and risk of falls. In addition, the LC Child-Pugh class and MELD score will be evaluated in order to determine BFR-RT safety and effects on the disease’s symptoms. To our knowledge, this will be the first intervention study to investigate BFR-RT in this population. Considering that current evidence shows BFR-RT is a safe method, even for frail populations [15, 17, 18], we believe BFR-RT will result in important increases in muscle mass and strength, accompanied by increases in functionality, with no negative outcomes on cirrhosis condition. There are some limitations to this study. The limited follow-up period prevents us from drawing conclusions about the long-term effects of the proposed intervention. Second, we opted to limit our sample to patients without severe LC complications (i.e., Child-Pugh class B and C and MELD > 15), limiting our ability to generalize our results to patients with decompensated LC.

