**Methods:**

Thirty participants will be randomly distributed between 1) BFR-RT and 2) control (CTRL). Assessments will occur at three time points: before the training intervention (0 W), after 12 weeks (12 W), and at follow-up (24 W). The following variables will be assessed: Child-Pugh classification; MELD score; SF-36 questionnaire; fatigue severity index; 6-min walk test; timed-up and go; 30-s sitting and rising test; dietary record; one-repetition maximum (1-RM) strength test (knee extension exercise); and vastus lateralis’ cross-sectional area, Pennation angle, and fascicle length. The BFR-RT group will undergo 12 weeks of knee extension exercise (1 × 30 repetitions and 3 × 15 repetitions at 20% 1-RM and 50% of total blood flow occlusion pressure), with two sessions per week. Data normality will be assessed using the Shapiro-Wilk test. In case of normal distribution, a one-way repeated measures analysis of variance will be implemented to test for differences in baseline values. A mixed model then will be applied for each dependent variable. In case of non-normal data distribution, a Kruskal–Wallis test will be implemented to test for differences in baseline values. Next, the Friedman test will be used to analyze repeated measures. Within- and between-group effect sizes will be calculated using Cohen’s *d* for each outcome. Finally, the minimal clinically important difference will be analyzed with distribution-based methods.

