In this sense, evidence shows that low-load RT combined with partial blood flow restriction (BFR-RT) results in significant muscle mass gains, comparable to high-load RT [15, 16] or low-load RT to muscle failure [17]. Its applicability in frail populations (e.g., elderly and cardiac patients) also has been verified, with positive outcomes after the intervention period [15, 18, 19], including functional performance [20]. Additionally, BFR-RT has been found to result in significantly smaller increases in systolic blood pressure, diastolic blood pressure and heart rate than both low-load RT and high-load RT performed to failure [21]. Thus, BFR-RT could prove to be a safe RT method in LC patients, improving muscle strength and mass while avoiding marked increases in blood pressure and, possibly, in portal pressure and variceal bleeding.

Thus, this study aims to investigate the effects of BFR-RT on muscle strength, muscle mass, fiber Pennation angle, fascicle length, functional performance, and risk of falls in LC patients. Additionally, we aim to verify whether BFR-RT is a safe method for this population. Our hypothesis is that BFR-RT will promote increases in muscle strength, muscle mass, and functional performance, while reducing the risk of falls, with no aggravation in LC condition.

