### Randomization

Initially, all participants will be pooled into a single group. This group then will be organized into quartiles according to participants’ initial 1-RM and vastus lateralis CSA. Next, participants in each quartile will be allocated to either the training (BFR-RT) or control group (CTRL) using a maximally tolerated imbalance model [22]. An unpaired T test will be applied to ensure no baseline difference between groups. If significant between-groups differences are detected, the randomization procedure will be repeated until a random distribution with no significant difference is achieved. The Berger-Exner test will be performed during data analysis to verify for selection bias [23].

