### Secondary outcomes

#### Child-Pugh class and MELD score

Participant blood samples will be collected and analyzed in a professional clinical laboratory. To classify these samples according to Child-Pugh class and Meld score at 0 W, 12 W and 24 W, they will be screened for aspartate aminotransferase, alanine aminotransferase, creatinine, albumin, and bilirubin. Additionally, clinical screenings will be carried out by a medical professional at the same time points for physical assessment of the participants.

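### Safety is a stated aim, but MELD and Child-Pugh get only efficacy-style difference tests and no adverse-event outcome is listed, so the analysis cannot support a claim of safety or no worsening

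*Protocol article*

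**What the plan says.** The Background of the protocol article states that "we aim to verify whether BFR-RT is a safe method for this population" and gives the hypothesis that the gains will come "with no aggravation in LC condition". The Aims section lists "Verify whether BFR-RT results in adverse events in LC patients". The Design overview describes the study as one of efficacy and safety.

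The measure appears in the Discussion: "the LC Child-Pugh class and MELD score will be evaluated in order to determine BFR-RT safety". In the outcome sections, Child-Pugh class and MELD are secondary outcomes at 0 W, 12 W and 24 W, and "clinical screenings will be carried out by a medical professional at the same time points for physical assessment of the participants".

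Data analysis names the dependent variables as "Child-Pugh class, MELD score, SF-36 and FSS scores, dietary records, TUG, 6MWT, SRT, 1-RM, CSA, PA and FL". All receive one treatment: a mixed model with group and time as fixed factors, or, if the data are not normal, a Kruskal–Wallis test at baseline followed by a Friedman test for the repeated measures. Hommel-adjusted p values are calculated for every variable, and unadjusted values are reported beside them. Within-group and between-group Cohen's d are planned for each outcome, as is a distribution-based analysis of the minimal clinically important difference.

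**The concern.** A hypothesis of no worsening is answered by showing that any worsening is smaller than some stated amount. That takes a margin and an interval. The article gives the two safety scores a test for a difference, and a small trial can fail to find a difference whether or not one exists. Three features make this worse.

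- **Multiplicity.** The adjustment covers the safety scores together with the efficacy variables. It protects against false claims of benefit, but for a harm variable it makes harm harder to declare.
- **Non-normal route.** The Friedman test compares time points within participants and has no group factor, so on this route the article plans no between-arm test of safety. Child-Pugh class is a candidate for this route, because it is a coarse category and class C is excluded at entry.
- **Adverse events.** They are an aim in their own right, yet no outcome or analysed variable corresponds to them.

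The article presents this as the first trial of the method in cirrhosis, so a statement that it is safe may be relied on by others.

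**Working it through.** The article gives a target of 30 but no alpha, power, SD, expected event rate or safety margin, so there is no stated figure to reproduce. The check asks what a trial of this size could show about safety.

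**Inputs**
- Total of 30: "Thirty participants will be randomly distributed between" two groups (Abstract, Methods).
- About 15 per arm: an inference. The allocation is made "using a maximally tolerated imbalance model" within quartiles, with no ratio stated; 14 to 16 treated is plausible.
- Assumed: two-sided 5% level, no dropout, SD of the MELD comparison of 2 to 4 points, illustrative event rates of 5% and 10%.

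**1. Aims against measures**

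| Stated aim | Outcome listed | Analysis listed |
|---|---|---|
| No worsening of liver condition | Child-Pugh class, MELD | Difference test, Hommel-adjusted; no margin or interval |
| Adverse events | None | None |

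The clinical screenings at 0 W, 12 W and 24 W are described as physical assessment. The article does not call them adverse-event recording.

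**2. Zero events among the treated**

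The exact upper bound is 1 − a^(1/n), with a = 0.05 (one-sided 95%) or 0.025 (two-sided 95%).
- n = 15: 1 − 0.05^(1/15) = 18.1%; 1 − 0.025^(1/15) = 21.8%.
- n = 14 to 16, one-sided: 19.3% to 17.1%.

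The chance of seeing no event is (1 − p)^15: 0.95^15 = 46% at a true rate of 5%, and 0.90^15 = 21% at 10%.

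The number treated without an event that would exclude a rate p (one-sided 95%) is ln(0.05)/ln(1 − p), rounded up: 29 for 10% and 59 for 5%.

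**3. Precision for MELD**

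For a simple two-sample comparison, the half-width of the 95% interval is t(0.975, 28) × SD × sqrt(2/15) = 2.048 × 0.365 × SD = 0.75 SD.
- SD 2: 1.5 points. SD 3: 2.2 points. SD 4: 3.0 points.

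If the observed difference were zero, the interval would still reach a worsening of that size. The planned mixed model may give a somewhat different width.

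**4. Power of the difference test (noncentral t, 15 per arm)**

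| True worsening | Level 0.05 | Level 0.05/12 |
|---|---|---|
| 0.5 SD | 26% | 6% |
| 0.8 SD | 56% | 20% |

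The right-hand column is Bonferroni over the 12 listed variables, a worst case for Hommel.

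**5. Size needed to show no worsening**

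Per arm, n = 2 × (1.960 + 0.842)² / (margin/SD)², with one-sided 2.5%, 80% power and a true difference of zero.
- Margin 0.5 SD: 63 per arm. Margin 1.0 SD: 16 per arm.
- At SDs of 2 to 4, a 2-point margin therefore needs 16 to 63 per arm.

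**The case against.** The strongest reply is that a reader might infer more than the article says.

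- **Non-significance read as safety.** A reader might infer that the investigators will take a non-significant MELD or Child-Pugh test as proof of safety. The article says only that the scores will be evaluated. This stands. What remains is that difference tests are the only inferential route offered for a no-worsening hypothesis.
- **No adverse-event collection.** A reader might infer that the trial records no adverse events. An article condenses the full protocol, which is not shown, and neither are the SPIRIT checklist and the assessment schedule figure. This also stands. The finding is the mismatch, within the article, between an explicit aim and its own lists of outcomes and analysed variables.
- **More than p values is planned.** Unadjusted p values, Cohen's d and a minimal-important-difference analysis are all listed, and they help. But an effect size without an interval does not bound harm, and the article does not tie the distribution-based threshold to a safety judgement.
- **Bleeding.** A reader might take variceal bleeding as the reason for the trial and argue that the two scores would miss it. The Background is motivated by sarcopenia; bleeding explains why this form of training was preferred to others. How the scores would respond to a bleed is not something the article settles, so the point does not rest on it.
- **Size.** It would be too strong to say that a null result is close to guaranteed unless harm is large: unadjusted power is 56% at 0.8 SD.

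**Conclusion.** The point holds in a limited form. The article sets out to establish safety and to check for adverse events, names only Child-Pugh class and MELD for the purpose, and gives them efficacy-style tests with no margin or interval. No adverse-event variable is listed. A non-significant result from that analysis could not support a conclusion of safety or of no worsening, although the documents do not say that it would be read that way.

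At about 15 treated, a clean record would leave event rates of up to roughly one in five open, and the MELD comparison would be uncertain by about three quarters of an SD either way. The figures rest on equal arms without dropout, and the conversion to MELD points rests on the assumed SDs. The mismatch between aim and analysis depends on none of these.

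**What to change.** 1. Take Child-Pugh and MELD out of the Hommel family.
2. Report the BFR-RT minus CTRL difference in MELD and in Child-Pugh points at 12 W and 24 W with unadjusted 95% confidence intervals, whichever way the normality check falls. Read them against a worsening margin that the investigators fix before analysis, and accept that the answer may be inconclusive at 30 participants.
3. List adverse events as an outcome: participants with any event, and with the liver complications named in the Background, by arm with exact 95% intervals. State which events were recorded prospectively.
4. Reword the safety aim and the eventual conclusion as describing events and bounding their rate.

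The cost is a more modest safety claim and a small amount of extra analysis; no more participants are needed. Two limits should be acknowledged. Recruitment began in September 2018, so recording may not have been prospective for participants already treated. No sessions take place between 12 W and 24 W, so ascertainment in that period rests on the 24 W visit.

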### Eligibility criteria

Eligibility criteria are 1) liver cirrhosis diagnosed by histopathological evaluation, hepatic elastography, or by clinic, radiologic or endoscopic criteria and 2) age ≥ 18 and ≤ 70 years. Exclusion criteria are 1) less than 6 months of alcohol abstinence, 2) MELD score > 15, 3) Child-Pugh class C, 4) decompensated chronic diseases, 5) diabetes mellitus, 6) hepatocellular carcinoma or others neoplasia, 7) previous liver transplant, 8) severe ascites, 9) persistent hepatic encephalopathy, 10) coagulation disorders characterized as INR ≥ 1.5 or platelets ≤ 75.000, or 11) medical contraindications for physical exercise practice.

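### The eligibility list does not bar Child-Pugh class B, but the Discussion describes a sample without class B, so the article contradicts itself on who is studied

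*Protocol article*

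**What the plan says.** The Eligibility criteria section sets two inclusion conditions: "liver cirrhosis diagnosed by histopathological evaluation, hepatic elastography, or by clinic, radiologic or endoscopic criteria and 2) age ≥ 18 and ≤ 70 years". Neither restricts Child-Pugh class. The severity exclusions read "2) MELD score > 15, 3) Child-Pugh class C, 4) decompensated chronic diseases", and further items include "8) severe ascites, 9) persistent hepatic encephalopathy, 10) coagulation disorders characterized as INR ≥ 1.5", the last of these continuing with a platelet limit. Class B is not mentioned.

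The Discussion, listing the study's limitations, says the sample was limited to "patients without severe LC complications (i.e., Child-Pugh class B and C", with MELD above 15 as the last entry in the bracket, and draws from this the consequence "limiting our ability to generalize our results to patients with decompensated LC".

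Child-Pugh class is also a secondary outcome. The section on it gives the assessment times: "To classify these samples according to Child-Pugh class and Meld score at 0 W, 12 W and 24 W". The Data analysis section lists it among the dependent variables for the mixed model, and the Discussion says that it and MELD will be used to judge the safety of the intervention.

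**The concern.** Both statements are current text of one article, and they give different answers to a basic question: may a patient in Child-Pugh class B take part? Eligibility fixes who is exposed to the intervention and to whom the efficacy and safety results apply. A reader who relies on the Discussion would take the findings as evidence in class A only. A reader who relies on the exclusion list would take them to cover class B as well.

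The answer also changes what Child-Pugh class can show as an outcome. If only class A enters, every participant has the same value at 0 W and none can improve. If class B enters, class can move in both directions. The Trial status section says recruitment was still under way at submission, so the question bears on people being screened as well as on later reporting.

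**Working it through.** No sample size, power or error rate is involved, so the check is a comparison of texts.

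**1. What each section shuts out, by named severity grade**

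| Grade | Eligibility criteria | Discussion |
|---|---|---|
| Child-Pugh class B | not named | outside the sample |
| Child-Pugh class C | excluded | outside the sample |
| MELD above 15 | excluded | outside the sample |

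The two sets differ by one element, class B.

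**2. Can the wording be read so that they agree?**

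- *The bracket in the Discussion lists the patients who were included.* This fails, because class C and MELD above 15 are both exclusion criteria.
- *The bracket means only patients who meet all its conditions at once.* This fails, because nobody is in class B and class C together, and the eligibility list gives class C and MELD as separate exclusions.
- *The other exclusions remove class B in practice.* Severe ascites, persistent encephalopathy, the INR and platelet limits and the undefined item on decompensated chronic diseases may remove some class B patients. Nothing says that they remove all. If the item on decompensated chronic diseases were meant to cover advanced cirrhosis, the separate items for class C, severe ascites and persistent encephalopathy would be largely redundant.
- *Another section resolves it.* The caption of Fig. 2 and the section on Child-Pugh class and MELD score say only that class is screened and reassessed.

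**3. What follows for Child-Pugh class as an outcome**

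- Under the eligibility list, the possible values at 0 W are A and B. Later values can be better, the same or worse.
- Under the Discussion, the only possible value at 0 W is A. The baseline variance is zero, so a baseline comparison between arms has nothing to test and an effect size scaled by the baseline standard deviation is undefined. Class can then only stay the same or worsen.

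**4. How many participants are concerned**

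The article gives no class distribution. Each class B participant would be 1/30 = 3.3% of the target sample. The number of such participants is unknown, and no range can be derived from the text.

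**The case against.** The strongest reply is that the two passages do not have equal standing. The eligibility list is the operative rule, while the other text is a passing limitation sentence in a Discussion. A stray mention of class B there is the more economical explanation. The conflict touches no randomization step, neither primary outcome (1-RM strength and muscle cross-sectional area), no stated number and no analysis model. All of this stands, and it limits the weight of the point. It does not remove the point: the article does not show that the Discussion is the slip, and eligibility is a core element of any protocol.

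Several stronger readings are tempting and are not supported.

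- A reader might infer that, if class B is eligible, the limitation about decompensated cirrhosis is wrong. Class C, MELD above 15, severe ascites, persistent encephalopathy and the coagulation limits would all still be excluded, so the limitation would largely hold. Only the description in the bracket would be wrong.
- A reader might infer that class B could make up most of the sample. The article gives no basis for this, and the other exclusions would remove some class B patients.
- A reader might infer that patients with milder ascites or episodic encephalopathy are certainly being admitted. The wording of those two exclusions permits it, but the undefined items on decompensated chronic disease and on medical contraindications to exercise could catch them.
- A reader might infer that screening has followed the Discussion. Nothing in the article suggests so.

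**Conclusion.** The contradiction is real and confined to class B. It leaves the studied population, and so the reach of the efficacy and safety results, stated in two incompatible ways. It also leaves open whether Child-Pugh class can improve at all from 0 W. The number of participants affected is not determinable from the article. The conclusion rests on reading the eligibility list as complete for Child-Pugh class and the bracket in the Discussion as a list of those left out, which is the only reading found that fits its other two entries. No view is taken on which statement is the intended one. The point should be settled before results are reported, and preferably before enrolment ends. It does not threaten the primary comparison.

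**What to change.** Check the Eligibility criteria section and the limitation sentence in the Discussion against the ethics-approved protocol and against the baseline Child-Pugh class of everyone already enrolled. Then make the two agree.

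- **If the Discussion is the error:** correct its description of the sample and report baseline Child-Pugh class by arm. The limitation on decompensated cirrhosis can largely stay. The cost is one wording correction and a record check.
- **If the exclusion list is the error:** correct it through the approval process, identify any class B participants already enrolled, and state how they will be reported. Add that class is then constant at 0 W and can only stay or worsen, which limits its use as an outcome and safety measure. This costs more than a wording change, because it alters approved procedures during recruitment.

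A separate, cheap improvement applies under either answer: analyse the Child-Pugh score in points, alongside or instead of class. A mixed model on a two- or three-level class is insensitive to change.
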